## Abstract

**Background:**

Heel pain is a common foot disorder that causes pain and functional limitations. The prevalence of disabling foot pain will increase as the population ages. Previous studies have reported the positive therapeutic effects of electroacupuncture, warm needling, or the combination of both for heel pain but with limitations in the study methodologies. The current study is a rigorously designed randomized controlled trial that aims to evaluate the clinical efficacy and safety of electroacupuncture plus warm needling therapy in patients with heel pain.

**Methods/design:**

The study protocol describes a prospective, open-label, parallel-group, randomized controlled trial to be conducted in Hong Kong. Eighty patients aged 50–80 years who have reported heel pain and first-step pain equal to or exceeding 50 mm on the 100-mm visual analog scale (VAS) will be recruited. They will be randomly assigned (1:1 ratio) to the electroacupuncture plus warm needling therapy (i.e., treatment) group or the waitlist (i.e., control) group. The treatment group will undergo six treatment sessions in 4 weeks. The control group will receive no treatment during the study period. The primary outcome measure is a mean change in the first-step pain VAS score from the baseline to week 4. Secondary outcome measures include a mean change in first-step pain VAS score from the baseline to week 2, a mean change in Foot Function Index (FFI) subscale scores and the total score from the baseline to week 2 and week 4, and patients’ self-reported level of improvement at week 4. Additional week 8 follow-up assessments with first-step pain VAS and FFI measurements will be arranged for the treatment group. Any adverse events will be recorded throughout the study to evaluate safety. An intention-to-treat approach will be used to analyze the study results.

**Discussion:**

This study will provide evidence on the efficacy and safety of electroacupuncture plus warm needling therapy as an alternative treatment method for heel pain. The findings will determine whether the treatment protocol is efficacious in relieving pain and improving foot function among older adults with heel pain. The study will also provide information for subsequent large-scale randomized controlled trials in the future.

**Trial registration:**

Chinese Clinical Trial Registry, ChiCTR1800014906. Registered on 12 February 2018.

**Electronic supplementary material:**

The online version of this article (10.1186/s13063-019-3572-4) contains supplementary material, which is available to authorized users.

## Background

Heel pain is a common foot disorder and most commonly involves pain surrounding the calcaneus inferiorly or posteriorly [1]. The typical complaint is pain and tenderness under the heel that is worse during weight-bearing, especially in the morning and when first moving after a period of inactivity, and is associated with tenderness over the calcaneal tuberosity at the commencement of weight-bearing activities. There are a variety of potential underlying causes, and treatment varies depending on the cause [1].

Heel pain is a common foot condition treated by health-care providers [2]. It is estimated to affect 10% of the general population at some time during life [3]. The frequency of the onset of disabling foot pain increases with age, and the prevalence of disabling foot pain will increase as the population ages [4]. The population-level prevalence of plantar heel pain in adults aged ≥ 50 years is 9.1% and for disabling plantar heel pain is 7.4% [5].

The risk of developing heel pain increases with increasing body mass index (BMI) and age [6]. Increasing BMI and age are associated with chronic plantar heel pain [7–9]. Chronic heel pain is most commonly reported by overweight, sedentary people aged 40–60 years and can occur throughout life [10, 11]. It has a significant negative impact on foot-specific and general health-related quality of life [11, 12].

Many treatment options are available, such as manual therapy, stretching exercises, taping, casted orthoses, night splints, extracorporeal shockwave therapy, education and counseling for weight loss, therapeutic exercise, dry needling, corticosteroid injection, local anesthetic injection, and surgery, with varying levels of evidence [2, 6, 13]. However, the best way to manage heel pain remains inconclusive. Heel pain may be a condition for which conservative management can be quite effective [14].

Previous systematic reviews have shown some positive evidence supporting the effectiveness of acupuncture in terms of providing significant benefits and improving pain and foot function related to heel pain, although the findings are inconclusive [15, 16]. Acupuncture treatments are widely variable with no consensus on which modality is most effective. In real-world practice, multiple treatments and rationales have been documented, but no single approach is dominant [17].

Studies have shown evidence for electroacupuncture analgesia [18]. Moxibustion has also been used for thousands of years to regulate meridians or channels and visceral organs of the human body. This is an integral therapeutic modality of acupuncture that uses ignited moxa floss to apply heat to certain points or areas of the body surface for treating diseases [19]. Moxibustion, which includes warm needling, is an effective treatment option in traditional Chinese medicine for acute and chronic pain [20, 21]. During warm needling, heat from the burning of moxa is transmitted to the corresponding acupuncture point by radiation as well as by conduction via the shaft of the needle, thereby stimulating deep tissue within the acupuncture point while warming the acupuncture point on the surface [22].

Studies have shown positive therapeutic effects of electroacupuncture [23], warm needling [24], or the combination of both [25] for heel pain, but with limitations in the study methodology. Combining these two modalities may provide an advantageous synergy in treating heel pain. Therefore, a well-designed randomized controlled trial is necessary to explore and determine the efficacy and safety of these methods in treating heel pain. Considering the significance of health problems associated with heel pain, a carefully designed randomized controlled clinical trial is proposed.

## Methods/design

### Study objective and hypothesis

This study aims to explore the efficacy and safety of electroacupuncture plus warm needling therapy for treating heel pain among older adults in Hong Kong. The study will examine whether electroacupuncture plus warm needling therapy can reduce heel pain intensity and improve foot function for patients with heel pain. We hypothesized that electroacupuncture plus warm needling therapy is better than the waitlist control in reducing pain intensity and improving foot function for patients with heel pain. This hypothesis is based on the superiority of electroacupuncture plus warm needling therapy over the waitlist control.

### Study design and setting

This study is a prospective, nonblinded, parallel-group, randomized controlled trial with a 1:1 ratio of patients allocated to receive electroacupuncture plus warm needling therapy (i.e., treatment group) or those allocated to the waitlist control (i.e., control group, who will receive delayed active acupuncture treatment after a week 4 assessment). The trial will be conducted at Pok Oi Hospital—The Chinese University of Hong Kong Chinese Medicine Centre for Training and Research (Shatin). The study protocol was developed based on the Standard Protocol Items: Recommendations for Interventional Trials (SPIRIT) [26]. The SPIRIT 2013 checklist is presented in Additional file 1. The study design and reporting of the study will follow the recommendations of the Consolidated Standards of Reporting Trials (CONSORT) [27], the STandards for Reporting Interventions in Clinical Trials of Acupuncture (STRICTA) [28], and the STandards for Reporting Interventions in Clinical Trials of Moxibustion (STRICTOM) [29].

### Study population

This study will focus on individuals with heel pain who are 50–80 years old. The eligibility criteria were developed primarily to enroll the appropriate individuals and to exclude individuals with serious diseases or contraindications to the treatments.

### Inclusion criteria

Individuals will be recruited for the study if they satisfy all of the following criteria:Aged 50–80 yearsHeel pain that is characterized by worsening when standing or when walking after getting up in the morning; the pain is relieved after walking for a while and worsens after a long period of walking [30]Heel pain with marked tenderness at the plantar aspect and lateral aspect of the calcaneal tuberosity [30]Heel pain that is unilateral or bilateralPain that is acute or chronic, with the degree of heel pain experienced on taking the first few steps rating ≥ 50 mm on a visual analog scale (VAS) of 0–100 mm at the time of recruitmentAgree to sign the informed consent form

### Exclusion criteria

Individuals will be excluded if they possess any of the following criteria:Pain in another area that is more severe than the heel painLoss of plantar foot sensationOpen wounds, tumors, or skin ulceration on the painful heel (or heels) and surrounding areaDocumentation of a fracture or abnormalities at the painful heel (or heels) within 4 weeks that are unsuitable for the study treatmentsAcupuncture and/or moxibustion treatment for the same heel pain during the previous monthExpected ongoing co-interventions (i.e., medication or alternative treatments or both) during the study periodPrevious surgery to the painful heel (or heels) or are scheduled to have surgery during the study periodSevere needle phobiaKnown hypersensitive reaction after acupuncture and moxibustion treatment or an inability to cooperate with the acupuncture and moxibustion procedureDiagnosis of cancer of any nature within 5 yearsKnown severe disease of the heart, brain, lung, liver, kidney, or hematopoietic systemA cardiac pacemakerPregnancy, are breastfeeding, or are expecting to become pregnant during the study period (a pregnancy test will be performed for child-bearing women whose last menstrual period was beyond 28 days and who are not in menopause or have not undergone sterilization)Known severe psychiatric or psychological disorderOther factors that have been deemed unsuitable for participation, as assessed by the investigatorsEngagement in any other clinical trial during the study periodPending foot-related litigation or disability claimsLack of capability to understand and answer the questions posed by the assessors in the study

### Recruitment

Individuals will be recruited through posters on bulletin boards at all Chinese medicine centers, polyclinics, and mobile clinics under the management of Pok Oi Hospital, through social media, and by cross-referral from the Chinese medicine practitioners of these clinics. Individuals interested in participating in the study will be referred to or will self-approach Pok Oi Hospital—The Chinese University of Hong Kong Chinese Medicine Centre for Training and Research (Shatin) to undergo eligibility assessment. They will be prescreened through a telephone interview. Potential candidates for recruitment to the study will have a face-to-face interview arranged to confirm their eligibility. During the interview, investigators will explain the overall objectives and nature of the study, describe the informed consent process, and assess the candidates’ eligibility. After an individual voluntarily reviews and signs the informed consent form, information such as sex, age, height, weight, BMI, and medical history will be collected. In addition, baseline assessment of primary and secondary outcome measures will be administered. An independent staff person who is not involved in the study will thereafter randomly allocate the study participants to one of two groups. A schedule for the treatment procedure will be assigned. The study flow is shown in Fig. 1. Figure 2 presents the schedule of enrollment, interventions, and assessments.

**Fig. 1 Fig1:**
[figure not shown]
Flowchart of study procedures

**Fig. 2 Fig2:**
[figure not shown]
Schedule of enrollment, interventions, and assessments. ^1^Only the treatment group will undergo the week 8 assessment and visits for ± 4 days are allowed. VAS visual analog scale, GRC Global Rating of Change

### Follow-up visits

The acupuncture and moxibustion used in this study are based on traditional Chinese medicine theory and a review of the literature. A previous study [31] has shown that warm needling acupuncture has a synergistic and more effective analgesic effect than acupuncture without heat or than heat applied to the skin surface. The treatment group will undergo a total of six treatment sessions because previous articles and reviews have shown that six or more acupuncture treatments were significantly associated with positive outcomes [32, 33]. The treatment regimen in this study will involve six treatment sessions of electroacupuncture plus warm needling therapy within a 4-week period on a regular basis (i.e., one treatment session every 3–5 days). The treatments will be provided at no cost to the participants. Assessments and a questionnaire will be administered on the day of the treatment session at week 2 (i.e., after the third treatment), at week 4 (i.e., after the sixth treatment), and at week 8 (for longer-term treatment effect evaluation).

No intervention will be provided for the waitlist control group during the study period. The participants will be informed that they are required to visit the Chinese Medicine Centre at week 2 and week 4 for study assessments. Considering that heel pain is an annoying condition and may affect a patient’s daily life, it may not be appropriate to start treatment after a longer waiting period. Therefore, participants will be scheduled to receive six acupuncture treatments for heel pain for free at their own discretion after the week 4 study assessments. No week 8 study assessments will be arranged for the control group because that would not provide a valid comparison with the treatment group.

To promote subject retention and complete follow-up, the study investigators will make every reasonable effort to follow the participants for the entire study period and provide timely reminders to the patients regarding their treatment or assessment schedule. A designated telephone line will be provided to all study participants to report adverse events during office hours.

### Randomization and blinding

The treatment allocation into the electroacupuncture plus warm needling therapy or waitlist control groups of each eligible individual in the study will be determined by a randomization process. The random allocation to the two arms of the study will be achieved using Random Allocation Software [34] following a balanced 1:1 pattern (electroacupuncture plus warm needling therapy:waitlist control) with a block size of 10. This randomization process will be conducted by an independent staff person who is not involved in the study to guarantee concealment of the allocations. The information on the allocation list will remain strictly confidential. The allocations will be concealed and sequentially numbered; opaque, sealed envelopes will be used to contain the randomization assignments.

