### Statistical analysis

#### Sample size calculation

The sample size calculation will be based on the primary outcome and evaluated with the OpenEpi statistical program [58]. The sample size estimate is based on a two-arm normal design. A two-sided test with an α level of 0.05 and 80% power detects a minimally important difference of 19 mm with a standard deviation of 28 mm (first-step pain as measured by the VAS) [54]. With an assumed attrition rate of 10%, each group will require 40 individuals, which implies a total sample size of 80 individuals for the entire trial.

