## Discussion

Patients who experience heel pain often suffer from pain and functional limitations. The prevalence of disabling foot pain will increase as the population ages. Acupuncture and moxibustion have been used to treat pain and functional limitations of heel pain for many years with positive results. Several previous studies have shown the positive therapeutic effects of electroacupuncture [23], warm needling [24], or the combination of both [25] for heel pain. According to these studies, single or combination therapy decreased pain intensity and symptoms of pain in patients with heel pain. However, because of the limitations of the study methodologies, little scientific evidence exists supporting the effectiveness of the methods. Therefore, we designed our study with an adequate methodology that follows international guidelines and uses validated assessment tools.

The objective of treating heel pain is to improve the quality of life by providing pain relief and preserving a patient’s foot function. The present study is an open-label, two-armed, parallel-group, randomized controlled trial that is designed to investigate the efficacy and safety of the combination therapy of electroacupuncture plus warm needling for treating patients with heel pain.

One limitation of the study is the possibility of a high risk of bias with regard to blinding because we used a waiting list as the control instead of a sham procedure. Owing to the nature of the acupuncture and moxibustion interventions, neither the study participants nor the acupuncturists can be blinded to the allocation and treatment stages.

This rigorously designed evidence-based clinical trial will evaluate whether electroacupuncture plus warm needling therapy is efficacious and safe in relieving pain and improving foot function among older adults with heel pain in Hong Kong. The present protocol may demonstrate electroacupuncture plus warm needling therapy as an effective and safe treatment option for patients with heel pain. The results obtained in the proposed study will provide valuable information and a solid foundation for future larger-scale clinical studies on the same topic. The study will provide evidence to determine whether the treatment protocol, which involves the combination of acupuncture and moxibustion, could be a potentially effective treatment alternative for heel pain.

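### A single fixed block size of 10 in an open, single-centre trial would let enrolling staff who know it and track allocations predict up to about 13 of 80 assignments

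*Protocol article*

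**What the plan says.** The section Randomization and blinding sets 1:1 allocation "with a block size of 10". No other block size is mentioned and no stratification factor is described. An independent person generates and carries out the randomisation, the list is confidential, and assignments are held in numbered, opaque, sealed envelopes.

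Study design and setting states: "This study is a prospective, nonblinded, parallel-group, randomized controlled trial". It names one centre: "The trial will be conducted at Pok Oi Hospital" (the sentence goes on to name that hospital's Chinese medicine centre in Shatin). The Discussion accepts that "neither the study participants nor the acupuncturists can be blinded to the allocation and treatment stages".

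Under Recruitment, candidates are prescreened by telephone and then interviewed by investigators, who "describe the informed consent process, and assess the candidates’ eligibility". Consent and baseline measurement follow, and only then does the independent person allocate. The exclusion criteria include a catch-all that leaves unsuitability to the investigators' judgement.

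The sample size section gives the total: "each group will require 40 individuals, which implies a total sample size of 80 individuals for the entire trial".

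**The concern.** Concealment has two parts: nobody should be able to see the next assignment, and nobody should be able to infer it. The envelopes and the confidential list deal with the first. The second depends on the sequence. With one centre, apparently one sequence, a treatment that everyone can see being given or withheld, and one block length stated in the protocol, a person who counts can tell when one arm has used up its five places. From that point to the end of the block, every assignment is known.

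Staff who expect a given arm have two ways to act on it before allocation: the discretionary exclusion, and the timing of the interview. The primary outcome is self-reported first-step pain in an unblinded comparison, and the first between-group analysis named is a two-sample t test or rank-sum test. That analysis would not correct for differences between arms introduced at entry. The Discussion acknowledges bias from lack of blinding but not this separate route, which an open-label trial can reduce.

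**Working it through.** **Inputs.** Block size 10 and ratio 1:1 (Randomization and blinding), so m = 5 places per arm in each block. Total 80 (Sample size calculation), so 80/10 = 8 complete blocks. Open allocation and one centre (Study design and setting). Assumption: the observer knows the block size, knows where blocks begin, and has an ordered record of all earlier assignments.

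**The plan's own figure.** With a 19 mm difference, SD 28 mm, two-sided α 0.05 and 80% power, the normal formula 2 × [28 × (1.960 + 0.842)/19]² gives 34.1, so 35 per arm; 35/0.9 = 38.9, so 39. The exact t-test needs 36 per arm (power 81.0%), and 36/0.9 = 40. The stated 40 per group is reproduced, and eight blocks of 10 give exactly 40:40.

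**Certain allocations.** The last k assignments of a block are all known when they all go to the same arm. The chance of this is 2 × C(10 − k, 5)/C(10, 5):

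| k | Chance that the last k are certain |
|---|---|
| 1 | 1.000 |
| 2 | 0.444 |
| 3 | 0.167 |
| 4 | 0.048 |
| 5 | 0.008 |

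The sum is 1.667 per block, which agrees with the closed form 2m/(m + 1) = 10/6. Over 8 blocks this is 13.3 of 80 (16.7%). The minimum is 8, one per block. Simulation of 8 blocks gives a 95% range of 9 to 19. In a little under half of blocks (44%), two or more final assignments are certain; in the rest, only the last is.

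**Best guess.** Always naming the arm that is behind in the block gives m + 2^(2m−1)/C(2m, m) − 1/2 = 5 + 512/252 − 0.5 = 6.53 correct per block of 10. That is 65.3%, or 52.3 of 80 against 40 by chance. About 31 of 80 assignments (39%) can be called at odds of 2:1 or better.

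**Other fixed sizes, certain allocations out of 80.** Size 4: 20 × 1.333 = 26.7. Size 6: 13.33 × 1.5 = 20.0. Size 8: 10 × 1.6 = 16.0. A block of 10 is less predictable than any of these.

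**Randomly varied sizes.** This was simulated for 80 patients, with sizes equally likely and an observer who knows the set of sizes but not their order:

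| Sizes | Certain of 80 | Best guess correct |
|---|---|---|
| 10 fixed | 13.3 | 65.3% |
| 4, 6, 8 | 1.8 | 67.8% |
| 6, 8, 10 | 1.4 | 66.2% |
| 8, 10, 12 | 1.1 | 64.9% |

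Varying the sizes removes almost all certainty. It does little to the guessing rate, and the sets that include smaller sizes make that rate slightly worse.

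**Final imbalance.** With sizes 8, 10 and 12 the last block may be cut short at patient 80. In 40,000 simulated sequences the mean absolute difference between arms was 0.8 patients.

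**The case against.** A reader might infer that the investigators know the upcoming assignments, that many allocations are predictable, or that selection will occur. The documents support none of these.

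- **Knowledge is not documented.** The block size stands in a published protocol article. What enrolling staff were shown during recruitment is not stated, nor whether anyone keeps an ordered tally. The randomiser is independent and the list is confidential. Silence about withholding the block size does not show that it was disclosed. This stands, and it makes the figures upper bounds. The absence of stratification is likewise read from silence.
- **Many is too strong.** Even a perfect observer is certain of only about 1 assignment in 6, and a block of 10 does better than the smaller fixed sizes above. This stands.
- **Safeguards limit the scope for selection.** Consent, eligibility and baseline assessment precede allocation, and entry requires a numeric pain score. The documents give no basis for a bias in millimetres. This stands as far as it goes, but a prediction would act at or before the eligibility decision, so the order of steps does not remove the risk.
- **The remedy is partial.** Varied sizes leave the guessing advantage and cannot repair completed blocks. Recruitment was due to finish before 31 August 2019, and the number of patients remaining is not given. This stands and belongs in the recommendation.

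The objections do not reach the central point: envelopes and a confidential list give no protection against inference from open past assignments and a known, constant block length.

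**Conclusion.** The point holds in conditional form. If enrolling staff know the block size and follow earlier assignments, about 13 of 80 allocations (17%, at least 8) are predictable with certainty and the best guess is right 65% of the time. The protocol neither says that this happens nor prevents it, so the concern is a possible route to selection and not evidence of it. The calculation assumes a single unstratified sequence and a perfect tally; less knowledge means less predictability. The sample size is not in error, and the design does not contradict itself. This is a worthwhile, inexpensive improvement to how allocation is protected.

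**What to change.** While recruitment is open, complete the current block. Then have the existing independent staff member generate the remaining sequence with block sizes varied at random around the present one, for example 8, 10 and 12. Do not move to smaller sizes, which would raise the guessing rate. Record the new sizes only in a document withheld from everyone who screens, consents or enrols. Deleting the figure 10 from existing documents achieves little now that it is published, so the protection must come from the new, undisclosed sizes.

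For a full 80 patients, certain predictions would fall from about 13 to about 1. The gain for this trial is limited to the patients still to be randomised, and a guessing advantage of about 65% persists.

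Cost: a short amendment with ethics approval, a new list and envelopes, and a final difference between arms that averages under one patient. If recruitment has ended, state the fixed block size as a limitation in the trial report.
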